# Health economic evaluation of a nurse-assisted online eye screening in home healthcare to reduce avoidable vision impairment (iScreen): study protocol for a cluster randomized controlled trial

**DOI:** 10.1186/s13063-023-07882-0

**Published:** 2024-02-02

**Keywords:** Eye screening, Older adults, Home healthcare, Vision impairment, Cluster randomized controlled trial

## Abstract

**Background:**

Among older people undiagnosed and untreated vision impairment and blindness are common. The leading causes are uncorrected refractive errors and cataracts. Vision problems are associated with a lower quality of life, several health problems, and a higher chance of falling accidents and fractures. To eliminate avoidable vision impairment and blindness, targeted eye screening programs are recommended. Older patients, receiving home healthcare, have not yet been considered as a population at risk who could benefit from eye screening.

**Methods:**

A cluster-randomized controlled trial will be conducted to investigate the cost-effectiveness and cost-utility of online nurse-assisted eye screening in home healthcare, compared to care as usual, in reducing avoidable vision impairment. A healthcare and societal perspective will be used. The study will be performed in collaboration with several home healthcare organizations in the Netherlands. The online eye screening consists of near and distance visual acuity, followed by an Amsler grading test. Measurements in both groups will take place at baseline and after 6 and 12 months of follow-up. A total of 240 participants will be recruited. Older men and women (65 +), who receive home-based nursing and are cognitively able to participate, will be included. The primary outcome will be the change of two lines or more on the Colenbrander-1 M visual acuity chart between baseline and 12-month follow-up.

**Discussion:**

An eye screening for populations at risk contributes to the detection of undiagnosed and untreated vision impairment. This may reduce the health-related consequences of vision loss and the high economic burden associated with vision impairment.

**Trial registration:**

ClinicalTrials.gov NCT06058637. Registered on 27 September 2023.

**Supplementary Information:**

The online version contains supplementary material available at 10.1186/s13063-023-07882-0.

## Background

Age is an important risk factor for vision impairment and blindness [1, 2]. Due to aging of the world population, an increase in older people with vision impairment is expected in the upcoming years [2–6]. In 2020, 1.1 billion people had distance vision impairment or uncorrected presbyopia worldwide. By 2050, this is expected to rise to 1.8 billion people [2]. The older population residing in care institutions and receiving home healthcare in the Netherlands experience a high prevalence of blindness and low vision, ranging from 20 to 25% [7, 8]. This is in line with the global prevalence of moderate to severe vision loss or blindness, for individuals aged 70 years or older, which is 22% and 5%, respectively [3], as well as self-reported data from nursing home facilities across eight European countries, reporting a 19.5% prevalence [9].

Vision impairment in older people is associated with lower quality of life and barriers to participate in society [5, 10–12]. It can also lead to health problems such as depressive symptoms, falls, and fractures [6, 12–17]. Furthermore, older adults with severe vision impairment can experience difficulties in obtaining health information due to the way the information is presented. Access to health information is necessary for making healthcare decisions and to follow up on healthcare recommendations [18].

Worldwide, the main causes of vision impairment and blindness are uncorrected refractive errors and cataracts. Other important causes are age-related macular degeneration, diabetic retinopathy, and glaucoma [19–21]. Although both leading causes of vision impairment and blindness are treatable with cost-effective interventions [3, 5, 21], uncorrected refractive errors and cataracts still make up approximately 41% and 39% of all moderate to severe vision impairment, respectively [20]. In a study by Limburg et al. cataract was even the main cause (51%) of vision impairment among residents in care institutions in the Netherlands [22]. It was found that up to 34% of older people with vision impairment could benefit from having appropriate spectacles [12]. Another study demonstrated improvement in quality of life and depressive symptoms in adults living in nursing homes who received spectacle prescriptions within 2 months [23]. Cataracts can be easily treated by surgically replacing the cloudy lens content with an artificial intraocular lens. Studies have shown that cataract surgery yields a positive effect on vision-related quality of life in older adults living in nursing homes [24], and it reduces the risk of falls among older adults [17, 25].

Despite the fact that the main causes of vision impairment have been well-known for many years, a high level of undiagnosed and untreated vision impairment among older people still exists [11]. To tackle this issue, the World Health Organization (WHO) recommends not only low- and middle-income countries, but also high-income countries to create awareness and establish eye-screening programs for the prevention of avoidable vision impairment and blindness [26]. This may reduce the high economic burden associated with vision impairment as well. It has been considered meaningful, given the direct and indirect care needs of visually impaired older adults, to detect any avoidable vision impairment in people in care institutions at an early stage [1, 8]. In addition, older adults will benefit longer when vision problems are detected at an early stage [1].

Patients receiving home healthcare, as a partly dependent population living in the community, have not been considered as a population at risk that could benefit from eye screening [7]. As of 2021, 8% of older adults in the Netherlands between the ages of 65 and 75 received home healthcare and 30% of people 75 years and older [27]. A systematic review by Clarke et al. [11] demonstrated that eye screening in a general practice setting did not improve vision among older adults due to the fact that they often did not follow up on the offered intervention as a result of the tests. They suggested further research to improve intervention uptake after screening, with a particular focus on healthcare-dependent populations rather than focusing solely on low-risk community groups [11]. In turn, a recent cross-sectional pilot study in one of the largest home healthcare organizations in the Netherlands showed that simple eye screening by community nurses can help detect eye problems among a potentially vulnerable older population still living in a relatively independent setting [7]. Approximately 20% of the patients were referred for eye problems that had not been diagnosed previously, and of those, only half of them actually used their referral to go to their general practitioner (GP), an optician, optometrist, or ophthalmologist. Half of them presented with severe vision impairment. In most cases, the eye problems could be corrected with spectacles or cataract surgery. The study highlighted that without eye screening in the home healthcare setting, many eye problems would have been left undetected and untreated [1].

Considering the common issues with mobility among this older population, receiving home healthcare, and hence difficulties to visit care facilities, utilizing e-health tools for eye screening in the home setting can be particularly beneficial. Previous research demonstrated good agreement between a nurse-assisted online eye screening and traditional visual acuity measurements, in a home healthcare population [28].

As the prevalence of visual problems seemed high and the impact of visual problems in the older population receiving home healthcare indicated unfavorable additional health outcomes, eye screening can be an important preventive measure in this vulnerable population. Moreover, as diagnostic and treatment options are available, screening tools are reliable, the natural course of eye diseases can often be predicted, the need for screening has been acknowledged, and the population at risk has been determined; it seems evident, considering the WHO relevance criteria for screening for potential health issues [29] that eye screening should be considered. However, an important aspect to assure the relevance of eye screening and its subsequent intervention uptake according to these criteria has not yet been investigated. There are no studies available regarding cost-utility and cost-effectiveness explaining the benefits of screening from a societal perspective in terms of relevant health indicators. As part of a larger study in which we also study the individual, healthcare, and socio-political context of eye screening in home healthcare, we present a protocol of a cluster-randomized controlled trial (RCT) to investigate the cost-effectiveness and cost-utility of “iScreen,” a nurse-assisted online eye screening (in addition to usual care) in home healthcare settings, compared to care as usual (CAU), in reducing avoidable vision impairment.

## Methods

### Study design and ethical approval

We will perform a cluster RCT to compare online eye screening, in addition to CAU, versus CAU. The eye screening will be guided by community nurses. Cost-effectiveness and cost-utility will be studied from a healthcare and societal perspective, including the impact on physical and mental health. We will map healthcare costs over a period of 1 year. The study will be performed in collaboration with three Dutch home healthcare organizations. The study protocol was approved by the Medical Ethics Committee of Amsterdam University Medical Centers (Amsterdam UMC), location VUmc in Amsterdam, the Netherlands. This study protocol was written according to the “Standard Protocol Items: Recommendations for Interventional Trial” (SPIRIT) reporting guidelines [30]. The SPIRIT checklist is added as an Additional file 1.

### Patient involvement

Stakeholder perspectives have been explored to investigate willingness to incorporate eye screening. In our recent qualitative exploratory study, interviews with professionals (*n* = 22) and patients (*n* = 8) were conducted to gain insight into barriers, facilitators, and public support for the implementation of an online eye screening ([name], [name], [name], [name], [name], [name], et al: Facilitators and barriers for implementation of online nurse-assisted eye screening in home healthcare: a qualitative study, unpublished). Professionals and patients were optimistic about implementing the online eye screening and expressed its added value. They also provided relevant information on how to offer eye screening within home healthcare (e.g., by offering tailored guidance, improving user-friendliness, and providing clear referral trajectories), which we used to optimize our intervention ([name], [name], [name], [name], [name], [name], et al: Facilitators and barriers for implementation of online nurse-assisted eye screening in home healthcare: a qualitative study, unpublished).

At the 6 month time period of the RCT, all patients from the intervention group (*n* ≈ 120) will be involved in an extensive process evaluation using elements of the RE-AIM framework [31] and the Telemonitoring Acceptance Framework [32]. Patients will get the opportunity to share their experience with the online eye screening and the referral process.

If the eye screening proves to be cost-effective, the results of this study and previous research will be presented during an invitational conference with important stakeholders, of whom at least five patient representatives. We will actively discuss how to overcome the known barriers and to use facilitators. Together with stakeholders, we will formulate the final implementation strategy and operational plan.

### Sample size

Taking into account a potential dropout of one-third, the sample size calculation revealed that we need 120 participants in the intervention group (receiving eye screening in addition to CAU) and 120 participants in the control group (receiving only CAU). A team of community nurses who provide care to patients in a specific geographical area will form a cluster. We aim to include 10 clusters in the intervention group and 10 clusters in the control group, both with 12 subjects each (Fig. 1), but this may vary in practice depending on the willingness of patients to participate within one cluster. Based on these numbers, we will achieve 82% power to detect a difference between the group proportions of 0.15, having a clinically relevant change of two lines or more in visual acuity (primary outcome measure). The proportion in the intervention group is assumed to be 0.05 under the null hypothesis and 0.20 under the alternative hypothesis. The proportion in the control group is 0.05. The test statistic used was the two-sided *Z*-test (unpooled). The intracluster correlation was set at 0.02 [33], and the significance level of the test was set at 0.05. Based on previous research in older populations [34], we expect that we need to invite approximately 1000 patients to include 240 participants. Loss to follow-up of one-third means that 80 participants (approximately 40 in both trial arms) are allowed to dropout during the course of the study in order to estimate the abovementioned effect, which seems reasonable based on previous studies [34] (Fig. 1).

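### The stated 82% power does not follow from the article's own inputs: with one-third dropout they give about 79%, and with no dropout about 90%

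*Protocol article*

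**What the plan says.** All of the inputs stand in the Sample size section of the protocol article. It plans 10 nurse teams per arm with 12 participants each, so 120 per arm. On the effect it says "The proportion in the intervention group is assumed to be 0.05 under the null hypothesis and 0.20 under the alternative hypothesis", and "The proportion in the control group is 0.05". The test is a two-sided Z-test with unpooled variance, the intracluster correlation is 0.02, and "the significance level of the test was set at 0.05".

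The section opens by saying that a one-third dropout has been taken into account. It then claims: "Based on these numbers, we will achieve 82% power to detect a difference between the group proportions of 0.15". It closes by saying that "80 participants (approximately 40 in both trial arms) are allowed to dropout during the course of the study" while the effect can still be estimated. The natural reading is that 82% is the power left after that loss, with about 80 completers per arm.

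**The concern.** A power figure stated with its full set of inputs should be reproducible, and this one is not. The wording could refer either to the 120 enrolled per arm or to the 80 expected to complete, but neither gives 82%. So the stated power, or at least one stated input, is wrong.

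What is at stake is modest. The text tells readers that losing 80 participants still leaves 82% power. On the stated formula that loss takes the power just below 80%. The loss compatible with about 82% is nearer 30 per arm than 40. That matters for anyone who monitors retention against the tolerance in the article.

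**Working it through.** **Inputs (Sample size section).** p1 = 0.05, p2 = 0.20, k = 10 teams per arm, ICC = 0.02, two-sided alpha 0.05 (critical value 1.96). Enrolled: 12 per team. Completers after one-third loss: 240 − 80 = 160, so 80 per arm, or 8 per team on average.

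**Formulas.**
- Design effect: DE = 1 + (m − 1) × ICC, with m participants per team.
- Effective sample per arm: n_eff = k × m / DE.
- Unpooled variance term: v = 0.05 × 0.95 + 0.20 × 0.80 = 0.0475 + 0.16 = 0.2075.
- Power = Φ(0.15 / √(v / n_eff) − 1.96).

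**Attempt to reproduce 82%.**

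| Completers per team | Per arm | DE | n_eff | 0.15 / SE | Power |
|---|---|---|---|---|---|
| 8 (one-third loss) | 80 | 1.14 | 70.18 | 2.76 | 78.8% |
| 12 (no loss) | 120 | 1.22 | 98.36 | 3.27 | 90.4% |

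Neither row gives 82%.

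**Does the approximation explain it?** Keeping 80 completers per arm, ICC 0.02 and a two-sided test, other versions give:
- pooled variance: 77.2%
- continuity correction: 70.4%
- arcsine: 80.5%
- exact binomial at n = 70 per arm: 79.9%
- variance computed with both arms at 0.05: 92.4% (this is not the unpooled test that the article names)
- simulated unpooled Z-test on beta-binomial data, 10 teams of 8 per arm, design effect treated as known: 81.0% (200,000 runs)

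The arcsine and simulated figures come close, but none of these lands on 82%.

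**Which changed inputs give about 82 to 83%?**
- 90 completers per arm (9 per team): DE = 1.16, n_eff = 77.59, power 82.7%. This is a loss of 30/120 = 25%.
- 11 teams of 8 per arm: 82.5%.
- ICC 0.005 with 8 per team: 82.5%.
- No clustering with 80 per arm: 82.5% pooled, 83.8% unpooled.
- ICC 0.05 with 12 per team and no dropout: 82.6%.

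The first is of interest because 90 × (1 + 1/3) = 120, whereas a true one-third loss is 80 / (1 − 1/3) = 120. Inflating by one-third instead of dividing by two-thirds would therefore produce the figure. That origin is inference, because the article does not show its calculation.

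**Side check on the assumed 0.20.** The Background reports of the pilot: "Approximately 20% of the patients were referred for eye problems that had not been diagnosed previously, and of those, only half of them" used the referral. Carried over unchanged, 0.20 × 0.50 = 0.10 would reach eye care. If every one of them gained two lines, the intervention proportion would be 0.05 + 0.10 = 0.15 (simple addition) or 0.05 + 0.95 × 0.10 = 0.145 (independence). With n_eff = 70.18 the power is then 51.7% or 48.5%. At 20% referral, reaching 0.20 needs 0.15 / 0.20 = 75% of those referred (addition), or 0.15 / (0.95 × 0.20) = 79% (independence), to attend and gain two lines.

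**The case against.** The strongest reply is that the gap is small and partly an artefact of the closed-form approximation. Simulating the named test gives about 81%, within about a point of the claim. This stands, and it limits the point to a reporting correction. It does not rescue the figure, because the stated formula with the stated inputs gives 79%.

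A reader might infer three stronger things that the document does not support.

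- **That true power is 74 to 76%.** A t reference on 18 degrees of freedom gives 74.2%, and a simulated team-level t-test 75.8%. But the article names a Z-test for the calculation and a logistic GEE for dichotomous outcomes. Small-sample handling of 20 teams is commonly left to a fuller document. These figures describe another reference distribution and should not replace the stated power.
- **That 0.20 is out of reach.** The pilot arithmetic assumes the pilot's referral yield and uptake. The trial uses its own online tool and referral criteria and excludes people with a recent eye consultation, so its yield could differ in either direction. The intervention is also designed to raise uptake: nurse checks, motivational conversations at 2, 4 and 6 weeks, reimbursed examinations (Referral and intervention uptake) and training in motivational interviewing (Training community nurses; Discussion). The assumption is optimistic against the pilot and the article gives no derivation for it, but that is a judgement and not a demonstrated error.
- **That a null result would be badly over-read.** A difference of one to three points in power does not support this.

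**Conclusion.** The 82% is wrong as written. On the article's own inputs the power is about 79% with 160 completers and about 90% with no loss. The shortfall is about 3 points by the stated formula and about 1 point by simulation of the named test with a known design effect. At least one number in the section needs correcting, and the document does not show which.

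This rests on reading the 82% as applying after the one-third loss, as the section's opening and close indicate, and on equal team sizes of 8. The article itself says that team sizes may vary. The arithmetic is firm. The comment on the pilot is secondary and conditional on the pilot's referral and uptake rates carrying over.

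**What to change.** Do one of two things in the Sample size section:

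1. Restate the power as about 79% for 160 completers (80 per arm, 8 per team) under the stated Z-test.
2. If 82% is the intended figure, correct the input that was misreported. For example, say that about 82% needs about 90 completers per arm, so that about 30 per arm, not 40, may be lost.

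Optionally, add a sentence giving the basis for 0.20 and noting that the pilot's referral and uptake rates would give about 0.145 to 0.15, with power of about 48 to 52%, unless the planned measures raise uptake or the referral yield is higher.

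The cost is a change of wording and, under the first option, a slightly less favourable figure. Recruitment, design and analysis are unaffected.

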**Fig. 1 Fig1:**
[figure not shown]
Flowchart of the iScreen study

### Recruitment

Older patients from several home healthcare organizations in the Netherlands will be invited by their community nurse to participate. The community nurse will evaluate patients' eligibility using the inclusion and exclusion criteria (Table 1). Patients with terminal illnesses or patients receiving palliative home care will be excluded. Recruitment will take place in three waves by using three inclusion cycles between March 2023 and August 2024 or until the total number of study participants has been achieved. Potential participants may indicate their interest to participate in the trial by sending out a form with contact information to the research team at Amsterdam UMC. Next, the research team will contact them by telephone to answer questions about the study and inform the patient about the informed consent procedure. Patients who are interested in participating in the trial will sign the informed consent form. After providing informed consent, the additional inclusion and exclusion criteria (Table 1) will be assessed by the researcher by telephone and the baseline measurement will be performed.

**Table 1 Tab1:** Inclusion and exclusion criteria

Inclusion criteria
- Patients receive home healthcare for health problems
- 65 years or older^a^
- Understanding of the Dutch language (telephone assessment)
- Cognitive ability to participate in research (telephone assessment: six-item Mini-Mental State Examination score > 3) [35]
Exclusion criteria
- Terminal illness, palliative home care^a^
- Cognitively unable to participate in research (e.g., late-stage Alzheimer’s, Parkinson’s (telephone assessment: six-item Mini-Mental State Examination score ≤ 3) [35]
- Having received an optometric or ophthalmic consultation within the last 6 months^a^ (telephone assessment)

^a^Criteria will be verified by a community nurse

### Randomization

Teams of community nurses (clusters), which will participate in the cluster RCT, will be randomized to either the intervention (eye screening in addition to CAU) or control group (CAU). As there are differences in the number of participants a team is able to include, we will group participating teams into matched pairs on the basis of number of participants to prevent imbalance between the group sizes. One researcher (VR) will use Castor to randomize the clusters, by using block randomization. Randomization of the clusters will be stratified by home healthcare organization to stimulate regional heterogeneity and to equally divide the additional burden on the organizations. This will be done after the community nurse has invited patients to participate in the study. Due to the nature of the intervention, community nurses and participants cannot be masked. Research assistants, who will perform visual acuity measurements and administer questionnaires during the follow-up assessments, will be masked. Participants are asked not to disclose the nature of their treatment allocation during the follow-up assessments. The research team will regularly check whether a research assistant is still masked by asking to guess to which trial arm a participant is allocated. Allocation to the intervention or control group will be communicated with the community nurses by email by an unmasked researcher.

